### Criteria for withdrawal and termination

Per ethical imperatives safeguarding patient autonomy, subjects retain the prerogative to withdraw from the study at any juncture for any reason. For subjects electing withdrawal, the rationale must be meticulously documented and incorporated as an evaluative metric for trial cessation. Clinical investigators should fastidiously document the basis for trial termination and its pertinence to the study, with analysis of the potential impact of the endpoint event on study conclusions.

All primary data on study withdrawals and terminations will remain sealed for examination upon trial completion. Moreover, grounds for termination include: any adverse events arising during the study; comorbidities, complications, or physiological alterations precluding ongoing participation; poor treatment compliance; contraindicated interventions; missed visits; and unblinding events.

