### Treatment group

Sterile acupuncture needles of 0.30 mm diameter and 40 mm length were utilized (Hualun Medical Appliance Co, Ltd, Suzhou). The acupuncture points were identified and localized conforming to the World Health Organization’s standards. The prescribed acupoints were PC6 (Neiguan), EX-HN3 (Yintang), KI6 (Zhaohai), RN17 (Danzhong), HT3 (Shaohai), and SP6 (Sanyinjiao). EX-HN3, and RN17 were inserted to a depth of 5-10mm, while KI6, PC6, HT3, and SP6 were inserted perpendicularly until reaching 20-25mm depth. The acupuncture procedure consisted of: disinfecting the skin and instruments; needle insertion at the acupoints, rotating bidirectionally between 90°-180° at 60–90 rotations/min until Deqi sensations of numbness, fullness, soreness, and aching were elicited, quantified using the Chinese Modified Massachusetts General Hospital Acupuncture Sensory Scale (C-MASS). Each 30-minute acupuncture session incorporated manual stimulation for 1 minute every 10 minutes.

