### Control group

After performing the same sterilization procedures as the treatment group, the sham acupuncture group utilized blunt-ended needles (Hualun Medical Appliance Co, Ltd, Suzhou) of 0.30 mm diameter and 40 mm length to administer non-penetrative needling at non-acupoints (selected stimulation points close to the treatment group’s acupoints but outside the meridians and avoiding the distribution of the body’s nerves). Specific non-acupoints selection are shown in S1 Table. The treatment duration matched that of the treatment group, however the blunt needles (Fig 3) were only tapped lightly on the skin surface without tissue penetration or manipulation to elicit Deqi. Sham-needle stimulation was simulated for 1 minute at 10-minute intervals during the 30-minute treatment.

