### Primary outcomes

The Pittsburgh Sleep Quality Index (PSQI), comprising 19 self-rated and 5 hetero-rated items, will be employed to evaluate the primary outcome of global sleep quality over the past month across 7 components: sleep duration, sleep latency, sleep efficiency, sleep medication use, sleep disturbances, subjective sleep quality, and daytime dysfunction. PSQI will be assessed at baseline, after each 4-week treatment phase (weeks 4, 8, 12), and during follow-up at weeks 16 and 24.

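### The termination grounds (any adverse event, poor compliance, missed visits, unblinding) are worded as leaving the study, which can end the PSQI collection that the ITT analysis needs

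*Protocol article*

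**What the plan says.** The section Criteria for withdrawal and termination first gives participants the right to leave at any time, then lists further grounds. The list opens with "grounds for termination include: any adverse events arising during the study", with no severity threshold. It continues with "comorbidities, complications, or physiological alterations precluding ongoing participation" and ends with "poor treatment compliance; contraindicated interventions; missed visits; and unblinding events". On the records it says: "All primary data on study withdrawals and terminations will remain sealed for examination upon trial completion". The investigator must document the reasons, "with analysis of the potential impact of the endpoint event on study conclusions".

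Four other sections bear on the point:

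- **Primary outcomes:** PSQI is taken at baseline, then "after each 4-week treatment phase (weeks 4, 8, 12), and during follow-up at weeks 16 and 24".
- **Patients' safety and adverse events:** withdrawal for an adverse event is left to the investigator, depending on how severe the event is.
- **Statistical analysis:** everyone randomized enters the ITT analysis, whether or not they complete the study.
- **Sample size:** the calculation uses the PSQI score after the full course of acupuncture and allows for 20% loss to follow-up.

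**The concern.** Stopping treatment and stopping observation are different decisions, and this section does not separate them. An ITT comparison needs outcomes from everyone randomized, including those who attend poorly, have an adverse event or work out their allocation. If those events end a participant's time in the study, the missing PSQI scores belong to people selected by what happened after randomization.

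Several of the grounds may relate to arm or response:

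- **Adverse events.** In the acupuncture arm "KI6, PC6, HT3, and SP6 were inserted perpendicularly until reaching 20-25mm depth". The sham needles "were only tapped lightly on the skin surface without tissue penetration or manipulation to elicit Deqi". Needling adverse events may therefore differ by arm.
- **Unblinding.** Deqi is sought in one arm only, and the Limitation section accepts that it complicates participant blinding.
- **Compliance and missed visits.** The course is 36 sessions over 12 weeks. It is plausible, though the document does not show it, that a participant who feels no benefit attends less.

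A later analysis plan can choose how to handle missing scores, but it cannot recover scores that were never taken. The result would then rest on assumptions about the people removed.

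**Working it through.** **1. The plan's own sample size.** Inputs from Sample size: SD 3.24, difference 11.43 − 9.20 = 2.23, α = 0.05 (taken as two-sided, which fits the stated figure; one-sided gives 37), power 90%.

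n per group = 2 × [(1.960 + 1.282) × 3.24 / 2.23]² = 44.36, which the plan gives as 44. With 20% loss, 44 / 0.80 = 55 per arm and 110 in total. The allowance is 0.20 × 110 = 22 participants from all causes, leaving 88 = 2 × 44. The stated figure reproduces, and this point does not depend on any error in it.

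**2. Scores lost per terminated participant.** Post-baseline PSQI assessments fall at weeks 4, 8, 12, 16 and 24, five in all. If termination ends participation:

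| Terminated | Scores lost | Week-12 score lost? |
|---|---|---|
| Before week 4 | 5 of 5 | yes |
| Between weeks 4 and 8 | 4 of 5 | yes |
| Between weeks 8 and 12 | 3 of 5 | yes |

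If only sessions stop, the rule itself causes no loss.

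**3. A missed assessment as the trigger.** This assumes that one missed visit is enough; the article sets no threshold.

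| Missed visit | Lost with termination | Lost if assessments continue | Avoidable, at most |
|---|---|---|---|
| Week 4 | 5 | 1 | 4 |
| Week 8 | 4 | 1 | 3 |
| Week 12 | 3 | 1 | 2 |
| Week 16 | 2 | 1 | 1 |

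The last column is an upper bound, because it supposes that the participant attends every later visit.

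**4. What the 20% allowance covers.** Power with 55 × (1 − loss) per arm, difference 2.23 and SD 3.24:

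| Share of week-12 scores lost | Power |
|---|---|
| 0% | 95.0% |
| 20% (planned) | 89.8% |
| 30% | 85.5% |
| 40% | 79.8% |

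The 30% and 40% rows are illustrative, since the article gives no expected termination rate. The allowance keeps power near 90% up to 20% loss. It says nothing about who is lost.

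**5. How selective loss shifts a mean.** If a fraction f of one arm is lost, and their scores would have differed by g points from those retained, the observed mean of that arm is off by f × g. With f = 0.20 and g = 2 points, both assumed, the shift is 0.40 points, and 0.40 / 2.23 = 18% of the planned difference. Over f = 0.10 to 0.30 and g = 1 to 3, the shift runs from 0.1 to 0.9 points (4.5% to 40%). Equal f and g in both arms would cancel. Loss within the planned 20% can therefore still bias the comparison.

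**The case against.** The strongest reply is that no sentence says PSQI collection stops at termination, and that a condensed article may leave continued follow-up to the full protocol. The textual support is also uneven. The phrase about leaving the study concerns voluntary withdrawal, and the one about ongoing participation qualifies only the item on comorbidities and complications. Some grounds concern treatment, and elsewhere the section speaks of ending the trial itself. Grounds for termination may be permissive, and the safety section then supplies the working rule for adverse events, namely severity as judged by the investigator. The ITT sentence expects non-completers and keeps them. Reasons for leaving must be recorded and their effect on the conclusions examined.

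Much of this is fair, and it limits the claim. The list does not strictly contradict the safety section or the ITT rule, and the counts in steps 2 and 3 hold only if termination ends assessment.

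It does not remove the point. Poor compliance and missed visits are participant-level events, and the section calls the outcome study withdrawals and terminations, so leaving the study is the natural reading. If termination instead meant stopping the whole trial, any adverse event would be a ground for that, which also needs correcting. The severity rule softens only the adverse-event ground; compliance, missed visits and unblinding have no such qualifier. Recording reasons describes the loss without replacing the scores. The objection is to a rule the article states, not to a detail it leaves out.

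**Conclusion.** The concern holds as a badly fixed rule that should be corrected, with moderate confidence. Read naturally, the section allows participants to be removed from the study for post-randomization events that may relate to arm or response, and no section preserves their outcome assessment. Each participant terminated before week 12 would lose three to five of the five post-baseline PSQI scores, always including week 12.

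This rests on two assumptions: that termination means leaving the study, and that assessment then ends. The number of participants affected, and the size and direction of any bias, cannot be established from the document. The power and bias figures beyond the planned 20% loss are illustrations only. The sample size of 110 is not in question here.

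**What to change.** Amend Criteria for withdrawal and termination in three respects:

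1. State that the listed grounds may stop acupuncture sessions only.
2. State that every participant who has not withdrawn consent keeps the scheduled PSQI and safety assessments to week 24, including after missed visits, poor compliance or unblinding, and is analysed as randomized.
3. Tie the adverse-event ground to the severity-based investigator decision in Patients' safety and adverse events.

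The cost is a short amendment, plus the effort of carrying out already scheduled assessments in people who have stopped sessions. No extra patients are needed. Trial status says recruitment has begun, so the change helps only those participants not yet terminated when it takes effect.

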### Randomization procedure and allocation concealment

In this trial, block randomization will be employed with a block size of 10. The research coordinator will generate randomization numbers independently utilizing SPSS 24.0 software without contacting study participants. To ensure allocation concealment, sequentially numbered opaque sealed envelopes will be employed, with an assigned designee independently administering the randomization sequence. Subsequent to informed consent, a total of 110 patients will be randomly allocated in a 1:1 ratio to the treatment arm (acupuncture group) or the control arm (sham acupuncture group).

### Blinding

The allocation of groups will remain concealed from patients, evaluators, and data analysts. The acupuncture points and techniques will be comparable between the two groups. The control group will undergo sham acupuncture with a non-penetrating device mimicking the look of real needles to preserve blinding [29], see Fig 3. To evaluate the success of blinding, we will survey participants on their belief about receiving either genuine or sham acupuncture after the intervention. Due to the distinct nature of performing acupuncture, blinding the practitioners is not feasible.

**Fig 3 pone.0301827.g003:**
[figure not shown]
Schematic of the two groups of acupuncture and non-penetrating devices.

### Interventions

Participants will undergo 36 acupuncture sessions over 12 weeks, at a frequency of 3 treatments per week. Acupuncture shall be administered solely by licensed acupuncturists. They are required to receive training in standardized techniques including needle manipulation and point location.

### Treatment group

Sterile acupuncture needles of 0.30 mm diameter and 40 mm length were utilized (Hualun Medical Appliance Co, Ltd, Suzhou). The acupuncture points were identified and localized conforming to the World Health Organization’s standards. The prescribed acupoints were PC6 (Neiguan), EX-HN3 (Yintang), KI6 (Zhaohai), RN17 (Danzhong), HT3 (Shaohai), and SP6 (Sanyinjiao). EX-HN3, and RN17 were inserted to a depth of 5-10mm, while KI6, PC6, HT3, and SP6 were inserted perpendicularly until reaching 20-25mm depth. The acupuncture procedure consisted of: disinfecting the skin and instruments; needle insertion at the acupoints, rotating bidirectionally between 90°-180° at 60–90 rotations/min until Deqi sensations of numbness, fullness, soreness, and aching were elicited, quantified using the Chinese Modified Massachusetts General Hospital Acupuncture Sensory Scale (C-MASS). Each 30-minute acupuncture session incorporated manual stimulation for 1 minute every 10 minutes.

### Control group

After performing the same sterilization procedures as the treatment group, the sham acupuncture group utilized blunt-ended needles (Hualun Medical Appliance Co, Ltd, Suzhou) of 0.30 mm diameter and 40 mm length to administer non-penetrative needling at non-acupoints (selected stimulation points close to the treatment group’s acupoints but outside the meridians and avoiding the distribution of the body’s nerves). Specific non-acupoints selection are shown in S1 Table. The treatment duration matched that of the treatment group, however the blunt needles (Fig 3) were only tapped lightly on the skin surface without tissue penetration or manipulation to elicit Deqi. Sham-needle stimulation was simulated for 1 minute at 10-minute intervals during the 30-minute treatment.

### Primary outcomes

The Pittsburgh Sleep Quality Index (PSQI), comprising 19 self-rated and 5 hetero-rated items, will be employed to evaluate the primary outcome of global sleep quality over the past month across 7 components: sleep duration, sleep latency, sleep efficiency, sleep medication use, sleep disturbances, subjective sleep quality, and daytime dysfunction. PSQI will be assessed at baseline, after each 4-week treatment phase (weeks 4, 8, 12), and during follow-up at weeks 16 and 24.

### Secondary outcomes

Assessment of stable angina pectoris (SAP): SAP was evaluated at baseline, week 4, week 8, and week 12 using the Seattle Angina Questionnaire (SAQ) to quantify angina symptoms before and after treatment. Blood biomarkers of SAP: Fasting venous blood samples were collected from the cubital fossa on the start and final of the treatment period in both groups. Levels of C-reactive protein (CRP), lipoprotein-associated phospholipase A2 (Lp-PLA2), and cardiac fatty acid-binding protein (C-FABP) were assayed by an independent laboratory blinded to group allocation.Quality of life assessment using the 36-Item Short Form Health Survey (SF-36).Dosage of sleeping pills.Hamilton Depression Rating Scale (HAMD).Generalized Anxiety Disorder 7-item (GAD-7) scale.

### Data gathering and administration

At screening, study personnel initiated collection of data on individuals meeting eligibility criteria, encompassing demographics (age, gender, occupation, ethnicity, marital status), anthropometrics (weight, height), education level, risk factors, medical history, medication history, and vital signs. During the intervention, study data were collected and documented per protocol via electronic transcription of paper case report forms, with data entry within 1 week of each study visit using EpiData software (version 3.0). Logical validation and double data entry with verification were implemented to ensure accuracy. An independent data manager external to the study oversaw data entry, verification, security, and resolution of abnormal values beyond clinically expected ranges. Finally, the database was locked for analysis after sign-off by the study sponsor, principal investigator, biostatistician, and data administrator, with no further modifications permitted.

### Patients’ safety and adverse events

Safety assessments were conducted at each study visit including: vital signs (temperature, blood pressure, respiration rate, heart rate); routine blood and urine tests; liver and renal function tests; electrocardiography. All adverse events were monitored, managed, and reported according to standard operating procedures detailing time of onset, duration, severity, interventions, and outcome. Adverse events will be collected according to the standardized methodology Common Terminology Criteria for Adverse Events (CTCAE). Trial suspension or withdrawal would be determined by the investigator contingent on adverse event severity. Any serious adverse event must be reported to the principal investigator and ethics committee within 24 hours.

### Sample size

The Pittsburgh Sleep Quality Index (PSQI) score following the full acupuncture intervention regimen was utilized to determine the requisite sample size. Statistical significance was defined as α = 0.05 with a power of 90%. Based on a prior study, perimenopausal women with insomnia had mean±SD PSQI scores of 11.43±2.11 with sham acupuncture and 9.20±3.24 with manual acupuncture [30]. Using the sample size formula:

$$n=2\times {\left[\;\frac{\left(Z_{\alpha }+Z_{\beta }\right)\times \sigma }{\delta }\;\right]}^{2}$$

Using the larger standard deviation of 3.24, with δ = 11.43–9.20 = 2.23, β = 0.1, 1-β = 0.9, and α = 0.05. The resultant sample size required per group was 44. Allowing for a 20% loss to follow-up, the total sample size needed for the study was 110 participants.

### Statistical analysis

Group allocation will be concealed from the statistician. All randomized participants will be included in the intention-to-treat (ITT) analysis, regardless of study completion status. To ensure accuracy, double data entry will be performed. Statistical analyses will be conducted using SPSS 24.0. Continuous variables will be summarized as mean ± standard deviation or median (interquartile range). Between-group comparisons will utilize two-sample t-tests or Wilcoxon signed-rank tests for skewed data. Within-group baseline to endpoint changes will be analyzed by repeated measure analysis of variance (ANOVA), with a primary focus on assessing interactions between groups and time. Categorical variables will be compared using Fisher’s exact or Chi-square tests. Statistical significance will be defined as p<0.05.

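### The methods named for PSQI do not, as written, deliver the promised analysis of all randomized women when scores are missing

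*Protocol article*

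**What the plan says.** The Statistical analysis section sets the population: "All randomized participants will be included in the intention-to-treat (ITT) analysis, regardless of study completion status". It then names the methods for continuous outcomes. For comparisons between arms: "Between-group comparisons will utilize two-sample t-tests or Wilcoxon signed-rank tests for skewed data". For change within groups from baseline to endpoint, the data "will be analyzed by repeated measure analysis of variance (ANOVA), with a primary focus on assessing interactions between groups and time". On software: "Statistical analyses will be conducted using SPSS 24.0".

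The Primary outcomes section gives six PSQI assessments: "PSQI will be assessed at baseline, after each 4-week treatment phase (weeks 4, 8, 12), and during follow-up at weeks 16 and 24". The Sample size section, which is based on PSQI after the complete course of treatment, expects losses: "Allowing for a 20% loss to follow-up, the total sample size needed for the study was 110 participants". The grounds for termination in the section on withdrawal include adverse events and end with "poor treatment compliance; contraindicated interventions; missed visits; and unblinding events".

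The article names no imputation method and no likelihood-based model.

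**The concern.** The same section fixes both a population and a set of methods, and the two do not fit together. The population is everyone randomized. In their usual form, the methods use only women with the scores they need. Taken literally, a PSQI result labelled intention-to-treat would describe the women who stayed.

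This matters if the women who leave differ from those who stay, and differ in another way in one arm than in the other. Adverse events, poor compliance, missed visits and unblinding are all listed as grounds for termination, and each could be related to arm or to outcome. The Limitation section also concedes that eliciting Deqi complicates participant blinding. Separately, a woman with PSQI scores at weeks 4 and 8 but not at week 12 would contribute nothing to the week-12 test, although her scores are informative.

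**Working it through.** **1. The plan's own figure.** Inputs from the Sample size section: SD 3.24, difference 11.43 − 9.20 = 2.23, α = 0.05, power 90%. Sidedness is not stated; two-sided matches and one-sided gives 37.

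n = 2 × [(1.960 + 1.282) × 3.24 / 2.23]² = 44.4 per arm (stated: 44). Then 44 / 0.80 = 55 per arm, or 110 in total. The stated figure reproduces, to rounding.

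**2. Women left at the planned loss.** 110 × 0.80 = 88, or 44 per arm. Because the inflation is applied to the end-of-treatment PSQI, 88 is the number the plan itself expects to have that score. If part of the loss falls only after week 12, a week-12 t-test would keep somewhat more, while an ANOVA that includes follow-up visits would not.

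**3. Power.** Power = Φ[2.23 / (3.24 × √(2/n)) − 1.960], with n per arm.

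| Loss | Women | Power |
|---|---|---|
| 0% | 110 | 95.0% |
| 10% | 99 | 92.8% |
| 20% | 88 | 89.8% |
| 30% | 77 | 85.5% |

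For n = 44: 2.23 / 0.691 = 3.228, and Φ(1.268) = 0.898. The inflation protects power at the planned loss.

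**4. The all-visits requirement.** The article does not say which visits enter the ANOVA. Suppose all five post-baseline visits do, and a share m of scores is missing independently at each (an assumption). The complete cases are then 110 × (1 − m)⁵, which is 99, 85 and 65 for m = 2%, 5% and 10%. These figures only illustrate how the requirement compounds. They should not simply be stacked on the 20%, because missed visits are themselves a ground for termination and may already be counted there.

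**5. Bias by algebra.** Let d be the dropout share in an arm, and k the number of points by which the dropouts' mean PSQI exceeds the completers' mean. The full arm mean is the completer mean plus d × k. The completer difference (sham minus acupuncture) is therefore too large by d_A × k_A − d_S × k_S. All values of d and k below are assumptions, apart from the overall 20%.

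| d_A | d_S | k_A | k_S | Bias (points) | Share of 2.23 |
|---|---|---|---|---|---|
| 0.20 | 0.20 | 2 | 0 | 0.4 | 18% |
| 0.20 | 0.20 | 2 | 2 | 0 | 0% |
| 0.25 | 0.15 | 2 | 2 | 0.2 | 9% |
| 0.15 | 0.25 | 2 | 2 | −0.2 | −9% |

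**6. Bias by simulation.** Assumptions: no true effect, SD 3.24, mean 11.43 in both arms, about 20% loss per arm.

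- Acupuncture women scoring above 13.5 at week 4 or 8 leave with probability 0.5, and sham loss is random. At visit correlation 0.5, completers show 0.41 points in favour of acupuncture at week 12. Varying the assumptions gives 0.26 to 0.54: 0.26 / 2.23 = 12% and 0.54 / 2.23 = 24%.
- The same mechanism acting in both arms gives 0.01.
- With acupuncture loss of about 21% rising with the week-4 score, random sham loss of 20% and correlation 0.6, the spurious difference is about 0.37 and the t-test rejects in about 8% of trials instead of 5%.
- A likelihood model using all observed visits brings the bias to about zero in the first scenario. This holds by construction, because dropout there depends only on observed scores. If dropout depends on the unseen week-12 score, such a model reduces the bias but does not remove it.

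**The case against.** The strongest reply is that the article is only silent on missing data. T-tests and ANOVA can be run on imputed data, nowhere does the article say that women with missing scores will be excluded, and such detail is commonly left to a statistical analysis plan that is not shown here. That stands, up to a point. A reader might infer that the trial will report a completer analysis; the documents do not support this, because imputation is not ruled out and the stated commitment is the opposite. Silence alone would not be a finding. What remains is that a population and methods are both stated, and the methods meet the commitment only with a further step that is not named.

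Three more points stand. A t-test loses only women missing the visit tested, not everyone with any gap. A reader might conclude that a quarter or more of the sample would be discarded, but that needs sporadic missingness assumed on top of the 20%, for which the documents give no figure. A reader might also take about half a PSQI point as the expected bias. That is the upper end of scenarios in which dropout is outcome-related in one arm and random in the other, and nothing in the documents establishes that asymmetry.

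A reply that does not stand is that equal dropout rates would be protection enough. In the first row of the algebra both arms lose 20%, and bias arises because the reasons for leaving differ.

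**Conclusion.** The point holds in a limited form. As written, the named methods do not deliver an analysis of all randomized women, and at the planned 20% loss the primary PSQI comparison would use about 88 of 110 at most. The sample size and its power of about 90% are unaffected.

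The risk is bias, together with unused partial data. Its size and direction cannot be derived from the documents. It is roughly 0.3 to 0.5 points (12% to 24% of 2.23) under assumed outcome-related dropout in one arm only, and about zero if dropout behaves alike in both. The case for changing the plan rests on the mismatch in the text and on a better method being available in the software already named, not on a forecast of bias.

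**What to change.** For PSQI, replace repeated-measures ANOVA with a linear mixed model for repeated measures (SPSS MIXED) using all observed visits, with arm, visit, arm-by-visit and baseline PSQI. Name the week-12 arm contrast as the primary comparison. Add a multiple-imputation sensitivity analysis that includes every randomized woman and allows for data not missing at random, for example by making the imputed scores of dropouts progressively worse.

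The cost is a few sentences and some extra programming in the same software, with no change to sample size, visits or treatment. The main model relies on data being missing at random; the sensitivity analysis shows how far the result depends on that. The change should be made before the database is locked and allocation is revealed to the statistician.

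### The Statistical analysis section names the Wilcoxon signed-rank test, a paired test, for comparing two independent arms on skewed outcomes; it should name the rank-sum test

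*Protocol article*

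**What the plan says.** All statements are in the protocol article.

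- **Between-arm test (Statistical analysis).** "Between-group comparisons will utilize two-sample t-tests or Wilcoxon signed-rank tests for skewed data". The signed-rank test is offered as the skewed-data counterpart of the two-sample t-test.
- **Within-arm change (Statistical analysis, next sentence).** "Within-group baseline to endpoint changes will be analyzed by repeated measure analysis of variance (ANOVA"), with the main interest placed on the group-by-time interaction.
- **Design (Randomization procedure and allocation concealment).** "block randomization will be employed with a block size of 10", with 110 patients allocated 1:1 to acupuncture or sham. No matching or crossover is described.
- **Sample size.** The formula is the one for two independent means, based on "mean±SD PSQI scores of 11.43±2.11 with sham acupuncture and 9.20±3.24 with manual acupuncture".
- **Outcomes that might be skewed (Secondary outcomes).** "Levels of C-reactive protein (CRP), lipoprotein-associated phospholipase A2 (Lp-PLA2), and cardiac fatty acid-binding protein (C-FABP) were assayed"; the dosage of sleeping pills is also listed.

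The article nowhere names a rank-sum or Mann-Whitney test.

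**The concern.** The signed-rank test works on differences within pairs. A participant in the acupuncture arm has no natural partner in the sham arm, so the named test does not fit the comparison it is assigned to. The same sentence gives the unpaired t-test as the parametric option, so its two halves assume different data structures.

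This is more than a detail left to a statistical analysis plan, because the article does name a test and it is the wrong one. For any outcome judged skewed, an analyst would have to choose between forcing an inapplicable test onto the data and departing from the published plan after the data exist. The second course is easily defended, but it is better settled in advance.

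**Working it through.** **1. Are the arms independent?** The randomization section describes 1:1 allocation in blocks of 10. Blocks balance numbers over time; they do not create matched pairs. The sample size calculation treats the arms the same way. Its inputs are SD 3.24, difference 11.43 − 9.20 = 2.23, α = 0.05 and power 90%:

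n = 2 × [(1.960 + 1.282) × 3.24 / 2.23]² = 44.36 per arm

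The plan states 44 (strict rounding up would give 45). With 20% loss, 44 / 0.8 = 55 per arm, or 110 in total. The plan's figures are therefore reproduced by a two-sided formula for two independent means.

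**2. Could the signed-rank test be meant for something else?** The sentence concerns between-group comparisons, and the following sentence gives within-group change to repeated-measures ANOVA. The text leaves no paired comparison for the signed-rank test to serve.

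**3. What happens if it is followed literally?**

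*Unequal arms.* A paired test needs equal numbers. With 44 and 43 observed values the routine returns an error. It could be run only by discarding participants, which conflicts with the commitment to analyse everyone randomized. The plan allows 20% loss, so unequal observed arms are likely.

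*Equal arms, arbitrary pairing.* The article gives no distributions for the outcomes that might be skewed, so the shapes and shifts below are assumptions.

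| Assumed data | Observed per arm | Rank-sum power | Signed-rank power |
|---|---|---|---|
| Gamma (shape 2), shift 0.68 (about 0.48 SD) | 44 / 44 | 0.75 | 0.66 |
| Lognormal, shift 0.6 log-SD | 44 / 44 | 0.79 | 0.73 |
| Lognormal, shift 0.6 log-SD, 8 participants discarded | 48 / 40 | 0.76 | 0.66 |

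The gamma row used 5,000 replicates and the lognormal rows 3,000. A fresh run of 5,000 replicates per row gave 0.76 against 0.66, 0.77 against 0.71, and 0.77 against 0.67. Under these assumptions the loss is about 6 to 10 percentage points.

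*Type I error.* In the gamma setting with no difference between arms, rejection rates were 0.051 for both tests. This is expected: if the arms share one distribution, the difference between a randomly paired member of each is symmetric about zero.

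*Dependence on pairing.* In one simulated gamma data set with 44 per arm, 5,000 random re-pairings gave signed-rank p-values with a 95% range of 0.0016 to 0.036. The rank-sum test gave a single value, 0.011.

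**The case against.** The strongest reply is that this is a naming slip. The test stands beside the two-sample t-test in a sentence about between-group comparisons, so the two-sample Wilcoxon test was evidently intended and a competent analyst would run it. That is probably right, and it limits the practical harm. It does not make the published wording correct.

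The reply is also right about three stronger inferences that a reader might draw.

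- **That the signed-rank test would be run within each arm and the two results contrasted.** The document does not support this, since within-group change goes to repeated-measures ANOVA. Nor can the resulting error be sized from the article. With equal true change in both arms, the chance that one arm is significant and the other is not is 2p(1 − p), where p is the power within an arm. It ranges from 0 to 50% according to p. With an assumed mean change of −2 and SD 3.24 in 44 participants, p was 0.97 in simulation and the chance is 2 × 0.97 × 0.03, about 6%.
- **That skewed outcomes would have no valid comparison between arms.** This goes too far. The group-by-time interaction compares the arms and does not depend on the named rank test. It is available for the repeatedly measured PSQI and could serve the biomarkers taken at the start and end of treatment. ANOVA may suit heavily skewed data poorly, but that is a different matter.
- **That the false-positive rate would be inflated.** With equal arms and a pairing made without regard to outcome, it is not.

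It is also fair to say that skewness of the biomarkers or pill dosage is presumed; the article reports no distributions.

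**Conclusion.** The point stands in a narrow form. The article assigns a paired test to an unpaired comparison, and nothing elsewhere in it corrects this. That conclusion follows from the text and needs no simulation.

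The size is modest. It touches only outcomes that come to be judged skewed. For those, a literal reading means either no computable test without discarding participants, or a pairing-dependent p-value with some loss of power (0.66 against 0.75 in the main simulation, on assumed data). PSQI is not exempted from the switch to a rank test, but its group-by-time analysis is intact. So are the t-test and the sample size.

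**What to change.** In the Statistical analysis section, replace the signed-rank test with the Wilcoxon rank-sum (Mann-Whitney U) test for between-group comparisons of skewed data. Record the correction as a dated clarification before database lock and unblinding; the Trial status section says recruitment is under way, so this can still be done. If a separate statistical analysis plan exists, check that it names the same test.

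The cost is one phrase: no new data, no change to the total of 110, and no effect on trial conduct. Analysing the biomarkers on the log scale with adjustment for baseline would be a reasonable option, but it is a preference and is not needed to correct this error.
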